### Control variables

Data on the control variables will be collected during the survey visits and will include characteristics that are likely to be correlated with child growth outcomes and child’s milk intake. This includes variables such child’s sex, age and diet, parent’s education, household wealth index, milk’s nutrient content, pathogens in milk and child’s maize consumption.

A questionnaire will collect information about child, parent and household characteristics. Information on children’s diet comes from the 24-hour recall survey. We will control for children’s diets by calculating caloric intake variables from eight food groups: (1) Breastmilk, (2) Grains, roots and tubers, (3) Pulses, nuts and seeds, (4) Dairy products, (5) Flesh foods (meats, fish, poultry, organ meats), (6) Eggs, (7) Vitamin-A rich fruits and vegetables and (8) other fruits and vegetables.^26^ Additionally, we will collect detailed data on the non-standard recipe’s ingredients for all mixed dishes that were prepared at home and use standard recipes from the National Food and Nutrition baseline survey dietary data set to assess the amount of food consumed.^27^ The dietary surveys will be administered outside of major Ethiopian Orthodox fasting periods during which dairy household availability and consumption may decline sharply.^28^

One potential source of measurement error in linking food consumption to child growth is within-person variability in consumption. Since linear growth in young children depends on long-term dietary quantity and quality, the 24-hour recall method is imperfect for capturing variability in diets over time.^29^ To address this, we will conduct interim phone surveys every 6 months to ask caregivers about the 24-hour milk consumption and weekly recall of the child’s diet diversity, and assess basic milk production. These higher frequency measurements will be used to assess seasonality, variability, and to adjust for consumption variability in our analysis.

A subsample of 500 livestock feed samples will be collected for testing AFB_1_. Detection of AFB_1_ in feed samples will be achieved using the Helica Low Matrix Aflatoxin B_1_ competitive ELISA kit, manufactured by Helica Biosystems, Santa Ana, California, USA, listed under Catalogue Number 981BAFL01LM-96 and using procedures outlined by them.^30^

While estimating the child’s actual amount of milk intake, the dilution of milk by water, a common practice in the Ethiopian livestock sector, is a key concern. The level of dilution from water may not be captured accurately through a survey question, as farmers may under-report such information due to social desirability bias. To address this issue, we will test the milk samples for nitrogen content (approximating protein). The total nitrogen content of the milk will be determined by the Kjeldahl method.^31^

The milk samples’ nutrient composition will be obtained from an ongoing analysis of Ethiopian Food Composition tables. However, we will re-analyse randomly selected subsamples to check if their nutrient composition is similar to those reported in the Ethiopian Food Composition table. In brief, proximate composition analysis, moisture content, crude fibre, crude protein and total ash of milk will be determined; with official method numbers 925.09, 2001.11, 4.5.01, 920.169, and 923.03, respectively.^32^ The calcium content of milk will be measured at the EPHI laboratory using an atomic absorption spectrophotometer, following the method no. 985.35 for Ca.^32^ The milk samples will be analysed for pathogens *E. coli* and *Campylobacter* spp. using the general procedures outlined in the Food and Drug Administration’s Bacteriological Analytical Manual BAM^33^ and ISO 10272-1:2017 (*for Campylobacter* spp). We expect that the milk samples found in the study will contain a high number of microbial florae in its background and low numbers of *Campylobacter* spp.

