### Explanatory variables

Child’s milk consumption and AFM_1_ levels in milk are the key explanatory variables in this study. Child’s milk consumption will be measured through a 1-day quantitative multiple-pass 24-hour recall interview, consisting of four steps designed to enhance respondent’s recall accuracy.^24^ We will ensure that all days of the week are proportionately represented during the dietary recall, to account for day-of-the-week effects on food intake. We will also collect a second, non-consecutive day 24 hours recall (repeat), within 2–10 days of the first recall, from a randomly selected subsample of children to account for the day-to-day variability of dietary intake within individuals and for nutrients estimation.

At the baseline and the end-line visits, we will collect milk samples (2000 samples in two rounds). AFM_1_ testing in milk, analysis of dilution of milk, nutrients composition and pathogens testing (including *Escherichia coli and Campylobacter* spp) will be conducted at Ethiopian Public Health Institute (EPHI) laboratory following standard operating practices for handling, processing and storing samples.

AFM_1_ in milk samples will be detected by using a commercial ELISA kit (catering to catalogue no. 961AFLM01C-ULTRA), manufactured by Helica Biosystems of Santa Ana, California, USA.^25^ The methodology for conducting the test will be based on the manufacturer’s guidelines. Standards and samples of 200 µl will be replicated in precoated plates. The resulting mixture will be incubated for 2 hours, followed by washing and the addition of conjugates. After the completion of 15 min of additional incubation and subsequent washing, enzyme substrate of 100 µl will be added to each well, permitted to incubate for 15 min and afterwards stopped using 100 µl of stop reaction. Finally, optical density measurements will be taken at 450 nm for each microwell using a microplate reader. Calculation of AFM1 levels achieved by means of a logarithmic standard curve will require an R^2^ value of no less than 95%. The average results from duplicate readings will be used for the presentation of results.^25^

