### Data analysis

#### Empirical approach

Descriptive analysis will focus on computing frequencies and percentages for categorical variables and summary statistics (like means, medians SD, IQR) for summarising continuous variables. To determine the association between dairy consumption and growth outcomes in children 6–18 months of age at the baseline, we will specify a least squares regression model as:

(1)
$$Y_{iv}=\alpha +\beta_{M}M_{iv}+X_{iv}^{\prime }\delta +\varepsilon_{iv}$$

where 
$Y_{iv}$
 is the anthropometric outcome for a child *i* residing in enumeration area *v* measured at various time points. Variable 
$M_{iv}$
 measures the child’s milk intake at various time points. The regression controls for child, parent and household characteristics that are captured in vector 
$X_{iv}$
. These control variables are observable characteristics that are likely to be correlated both with a child’s milk intake and his/her growth outcomes. The terms 
α
 and 
$\varepsilon_{iv}$
 in equation (1) represent the intercept and error term, respectively. The coefficient 
$\beta_{M}$
 quantifies the conditional association between a child’s milk intake and subsequent growth outcome, measured either as HAZ at the end line or as change in HAZ between the baseline and end-line surveys. Considering previous evidence from Ethiopia and elsewhere, we expect 
$\beta_{M}$
 >0.

To determine the association between AFM_1_ levels in milk and nutrient density in milk, we will conduct a univariate analysis on each of the macronutrients and micronutrients and then carryout bivariate tests with AFM_1_ levels in the same samples and determine if and how they are associated with each other.

To determine the association between AFM_1_ exposure and growth outcomes in children 6–36 months of age who consume dairy, we will test whether the consumption of AFM_1_-contaminated milk is associated with lower HAZ (ie, more growth faltering) controlling for confounders and co-factors, including the amount of milk consumed and nutrient content and pathogens in the milk. We will append equation (1) with a variable capturing the child’s AFM_1_ exposure (variable 
$A_{iv}$
). In this model, we also control for the estimated macronutrient and micronutrient content and pathogens (vector 
$C_{iv}^{`}$
) in the milk sample collected at the baseline from the household in which the child resides. We will also control for the child’s maize consumption (vector 
$H_{iv}^{`}$

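### The diet controls include calories from dairy products without excluding milk, so β_M measures milk at fixed dairy calories, not the overall milk–growth association

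*Protocol article*

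**What the plan says.** Under Explanatory variables, the exposure is taken from a dietary recall: "Child’s milk consumption will be measured through a 1-day quantitative multiple-pass 24-hour recall interview". Under Control variables, diet is one of the named controls ("This includes variables such child’s sex, age and diet, parent’s education, household wealth index"), and its source is also a recall: "Information on children’s diet comes from the 24-hour recall survey". Diet is to be controlled for by "calculating caloric intake variables from eight food groups: (1) Breastmilk, (2) Grains, roots and tubers, (3) Pulses, nuts and seeds, (4) Dairy products", followed by flesh foods, eggs and two fruit and vegetable groups. Milk is not carved out of group 4.

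Under Empirical approach, M in equation (1) "measures the child’s milk intake at various time points". For the controls the text says: "The regression controls for child, parent and household characteristics that are captured in vector" X. The coefficient β_M is said to be one that "quantifies the conditional association between a child’s milk intake and subsequent growth outcome", and it is expected to be positive. Equation (2) keeps M and X and adds AFM1 exposure, milk content and maize. The benefit–risk comparison is a joint test, from equation (2), that β_M and β_A are both zero.

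**The concern.** Milk is a component of dairy calories. Once dairy calories are in X, the exposure is partly on both sides of the adjustment. The remaining contrast is between children who differ in milk intake but have equal dairy energy.

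β_M carries the first objective (milk consumption and growth) and the benefit side of the third (benefits against risks). If milk helps growth mainly through the energy it supplies, this model would credit that benefit to a control variable. The study could then report little or no milk benefit when one exists. The study is meant to inform regulation of AFM1 in milk, so understating the benefit side matters.

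**Working it through.** The plan gives no figure for this point: neither the correlation between milk intake and dairy calories nor the share of dairy energy from non-milk foods. The sample size of about 1000 does not bear on it. The check is therefore algebra, followed by a range under stated assumptions.

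**1. What β_M means.** Let D be dairy calories, with D = kM + O, where k is energy per unit of milk and O is energy from other dairy. With D in X, and γ its coefficient:

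Y = α + β_M·M + γ·D + … = α + (β_M + kγ)·M + γ·O + …

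The association of milk with growth, holding other dairy fixed, is β_M + kγ. The plan interprets and tests β_M alone, so the part kγ is lost from the reading. If k varies between children, for example through dilution with water, β_M also picks up volume at fixed energy.

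**2. Precision.** Adding D multiplies the variance of β_M by VIF = 1/(1 − r²), where r is the correlation of M with D given the other controls. The SE is multiplied by √VIF. For a test with two-sided 5% level and 80% power before D is added, power becomes Φ(2.802/√VIF − 1.960), with 2.802 = 1.960 + 0.842. This takes the coefficient itself as unchanged.

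| r (assumed) | VIF | SE multiplier | Power |
|---|---|---|---|
| 0.7 | 1/(1 − 0.49) = 2.0 | 1.40 | 52% |
| 0.9 | 1/(1 − 0.81) = 5.3 | 2.29 | 23% |
| 0.95 | 1/(1 − 0.9025) = 10.3 | 3.20 | 14% |

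**3. Bias relative to the intended quantity.** This was simulated with 900 children (1000 less 10% attrition), 500 replicates per scenario, normally distributed intakes, and a total milk effect of 0.10 outcome SD per SD of milk. Entries are the mean estimate, with the mean SE in brackets.

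| r | Share of effect through dairy calories | β_M without D | β_M with D | Rejection rate, without / with D |
|---|---|---|---|---|
| 0.71 | all | 0.101 (0.034) | −0.002 (0.047) | 84% / 4% |
| 0.71 | half | 0.101 (0.033) | 0.051 (0.047) | 85% / 23% |
| 0.71 | none | 0.103 (0.033) | 0.104 (0.047) | 84% / 59% |
| 0.89 | all | 0.105 (0.033) | 0.005 (0.075) | 87% / 5% |
| 0.89 | half | 0.099 (0.033) | 0.049 (0.075) | 84% / 11% |
| 0.95 | all | 0.103 (0.033) | 0.011 (0.107) | 86% / 6% |

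The loss in β_M follows the share that runs through calories, as step 1 predicts, whatever the correlation. The SE ratios (0.047/0.033 = 1.4, 0.075/0.033 = 2.3, 0.107/0.033 = 3.2) agree with step 2.

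**4. If M is averaged over rounds.** The plan intends to use the phone rounds to adjust for variability in consumption. Suppose M is the mean of four exchangeable occasions, D is dairy energy on one of them, and no other dairy is eaten. Then r² = ICC + (1 − ICC)/4. An assumed ICC of 0.3 gives r² = 0.475 and VIF = 1/0.525 = 1.9. An ICC of 0.7 gives r² = 0.775 and VIF = 1/0.225 = 4.4. The inflation is then moderate, but β_M is still conditional on dairy calories.

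**The case against.** The best defence is that this is a condensed article. Empirical approach describes X as characteristics related to both milk intake and growth. That describes confounders, not the exposure itself, and the eight groups are not listed one by one in the equations. A full protocol might leave dairy out. This explains how the overlap could have been overlooked, but does not remove it: Control variables names diet as a control and defines it by a list that includes dairy. An analyst following the article would include it. This is a stated covariate, not an omitted detail.

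It can also be said that nothing is lost for good. With milk in calories, the sum of the milk and dairy coefficients from the same fit gives the milk association at fixed other dairy. That is correct, and it is why the repair is cheap. The plan, however, reads and tests β_M, not that sum.

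Several stronger readings are tempting, and the document does not support them:

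- **β_M cannot be estimated.** This needs exact proportionality of milk and dairy calories across the sample. Other dairy foods, dilution or averaging over rounds would break it.
- **β_A is destabilised too.** AFM1 exposure is not defined as a dose. Even when simulated as milk times an independent concentration, its VIF was the same with and without dairy calories (1.225 both ways at a 5% non-milk share of dairy energy, 1.236 both ways at 20%), because M is already in the model.
- **Maize is double counted in the same way.** The plan says "We will also control for the child’s maize consumption", and maize also belongs to group 2. But both terms are controls. In the same units, maize with all grains spans the same space as maize with other grains, so β_M and β_A are identical either way.
- **The 0.3 SD detectable effect can be multiplied by the SE factor.** That figure is tied to an association with household cow ownership, not to a coefficient per unit of milk, so the scales do not match.

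**Conclusion.** Wrong as written. With dairy calories among the controls, β_M in equations (1) and (2) does not answer the first objective, and the joint test weighs AFM1 risk against something other than the benefit of milk. This follows from the listed covariates alone and needs no numerical assumption.

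The size does need assumptions. The part of the milk association that runs through dairy calories drops out of β_M: all of it if energy is the whole pathway, half if it is half. If none runs through calories, β_M keeps its value and only precision suffers. The variance inflation depends on a correlation that the article does not give, so the tabulated values are illustrations, not estimates for this cohort.

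**What to change.** State in the protocol or analysis plan that, in equations (1) and (2), the diet controls exclude the dairy group, or that this group is limited to energy from dairy foods other than milk. Keep the other food groups as planned. With the second option, β_M is the milk association at fixed non-milk dairy. With the first, it also takes up any non-milk dairy intake that goes along with milk. The text should say which is intended.

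The cost is one sentence. No extra data, samples or participants are needed, since the recall already records the foods from which the groups are built, and the change can be made before the analysis.

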### Study timeline

For the main study, field activities will commence in April 2024 and all data collection activities will be completed by August 2025. Before the start of the quantitative survey, a 1-day stakeholder participatory meeting will be held to inform about the survey goals and seek consent to proceed with the study activities. Data management, monitoring and data analysis will be a continuous process throughout the study period. Results dissemination to the stakeholders will be carried out in December 2025.

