**Methods and analysis:**

This protocol paper describes our study in Sidama to determine the impact of milk consumption and AFM_1_ on child growth in the first 18 months of life. We will collect baseline and end-line data on dairy production, socioeconomic and nutritional factors of 1000 dairy-owning households with children ages 6–18 months at baseline; and gather samples of milk and dairy feed and child anthropometrics. We will conduct phone interviews every 6 months to ascertain changes in practices or child health. Dairy feed will be tested for AFB_1_; milk for AFM_1_, pathogens and nutrients. Controlling for herd size, socioeconomic, nutritional and behavioural factors, we will determine the association between child anthropometrics and milk consumption, as well as AFM_1_ exposure. We will examine whether AFM_1_ exposure affects child growth in the first 18 months of life, and weigh the benefits and risks of milk consumption.

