## Objectives

Our goal is to determine whether AFM_1_ exposure through milk consumption is associated with child growth impairment over a period of 18 months in early childhood; then to compare this risk with the benefits of milk consumption. This evidence will inform policy recommendations for AFM_1_ regulation in dairy products in Ethiopia. The specific objectives of this study are to:

Determine the association between milk consumption and growth outcomes in children 6–36 months of age.Examine the association between AFM_1_ exposure and growth outcomes in children 6–36 months of age who consume milk.Compare the health benefits and risks associated with dairy consumption in relation to child growth outcomes.Develop policy recommendations for regulating AFM_1_ and communicating dairy benefits and risks.

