### Study design and data collection

The target group of the main study is 1000 caregivers and their children aged 6–18 months from urban or peri-urban households that raise dairy cattle. In the initial visit, a baseline survey will be used to collect data such as anthropometric measurements, child’s diet and socio-demographic factors among other data. After the baseline survey, short phone-based interviews will be carried out every 6 months to assess the variability in the child’s milk consumption and dairy production factors. Our end-line visit, mainly to collect data on child’s anthropometric measurements, will be carried out 18 months after the initial visit. **Patient and public involvement**: the interview results from the formative research described above on public participants in Sidama, Ethiopia, aided the selection of households in the second part of our work.

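### The stated field period (April 2024 to August 2025) is at most 17 months, so the 18-month end-line visit cannot be reached for any child; the abstract also names an age window that the design does not cover

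*Protocol article*

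**What the plan says.** All places are in the protocol article.

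- **Interval.** Study design and data collection says that the end-line visit "will be carried out 18 months after the initial visit". Objectives gives the same length for the goal: "child growth impairment over a period of 18 months in early childhood". Between the two visits, "short phone-based interviews will be carried out every 6 months".
- **Calendar.** Study timeline, in a sentence that refers expressly to the main study, says "field activities will commence in April 2024 and all data collection activities will be completed by August 2025". It then adds: "Results dissemination to the stakeholders will be carried out in December 2025".
- **Age.** The target group is "1000 caregivers and their children aged 6–18 months from urban or peri-urban households". The objectives concern "growth outcomes in children 6–36 months of age". The abstract describes the effect of milk and AFM1 "on child growth in the first 18 months of life", and repeats that age window in its last sentence on methods.
- **Use of the end line.** Data analysis takes the growth outcome as HAZ at the end line or as the change in HAZ between the two surveys.

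**The concern.** The interval and the calendar are both explicit, and they cannot both be followed. One of them will give way in the field, and the article does not say which.

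The end-line visit produces the primary outcome. If the closing date governs, follow-up is shorter than stated and may differ between children by enrolment date. A change in HAZ would then cover intervals of unequal length. If the 18 months govern, the closing date moves and the time for analysis before dissemination largely disappears. The choice also sets the month of the second milk collection, and Sampling procedures reports that feed varied by season.

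The age wording is a separate matter. A reader of the abstract alone would take the study to be about growth from birth to 18 months. The design observes children from 6 months onward, and an 18-month end line measures all of them after 18 months of age.

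**Working it through.** **Inputs.** Start April 2024, close August 2025 and dissemination December 2025 (Study timeline). Interval 18 months (Study design and data collection; Objectives). Age at entry 6–18 months (Study design and data collection). The length of the baseline round is not given.

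**1. Longest and shortest field period.** Days between the dates, divided by 30.4375 days per month:

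- 1 April 2024 to 31 August 2025: 517 / 30.4375 = 16.99 months
- 30 April 2024 to 1 August 2025: 458 / 30.4375 = 15.05 months

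The plan's figure of 18 months is not reproduced on any reading of the stated months.

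**2. Due date of the first end-line visit.** Start + 18 months:

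- 1 April 2024 gives 1 October 2025
- 30 April 2024 gives 30 October 2025

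Both fall after 31 August 2025. Working backwards, 31 August 2025 minus 18 months is 29 February 2024, so every baseline visit would have to be finished before the stated start.

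**3. Last children enrolled.** Assume that baseline starts on 1 April 2024 and takes 2–3 months:

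| Assumed last baseline visit | Longest follow-up by 31 August 2025 | Due date at 18 months |
|---|---|---|
| End of May 2024 | 15 months | End of November 2025 |
| End of June 2024 | 14 months | End of December 2025 |

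As planned, 31 August to December 2025 leaves about 3–4 months before dissemination. With 18 months kept, the time left is at most about one month in the first row and none in the second.

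**4. Interim calls.** Calls at 6 and 12 months do fit: a baseline as late as 31 August 2024 reaches 12 months on 31 August 2025. Of the planned contacts before and at the end line, only the end-line visit is out of reach.

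**5. Age at end line.** Entry age + interval:

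- 6 + 18 = 24 months and 18 + 18 = 36 months, so 24–36 months at end line
- With the longest interval the calendar allows: 6 + 17 = 23 and 18 + 17 = 35 months

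The span observed over an 18-month follow-up is therefore 6–36 months, as the objectives say. The abstract's window agrees neither with that span nor with its own statement, in the same paragraph, that children are 6–18 months old at baseline.

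**The case against.** The strongest reply is that this is an administrative date and one phrase in an abstract. The sample size and the model equations do not use the dates, and the shortfall that is certain is only about one month in 18. That is fair as to size. It does not remove the contradiction, because the shortfall applies to every child. The formative phase cannot explain it either, since the timeline sentence is limited to the main study.

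Several stronger readings are tempting, and the document does not support them.

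- **Bias by recruitment month.** A reader might infer that later-enrolled children must have shorter follow-up. That would follow if all children were measured close to one closing date. About 1000 end-line visits also need a round of their own; if it repeats the baseline order, the interval is short but nearly equal for all. The article does not say which applies, so unequal follow-up is possible, not certain.
- **No adjustment for age.** HAZ is standardised for age by the WHO standards, and the child's age is a listed control. What stays open is only whether the interval enters the change-in-HAZ model if intervals differ.
- **Three conflicting age ranges.** The 6–18 and 6–36 month ranges agree: one is age at entry, the other the span over follow-up. Only the abstract's phrase conflicts.
- **A question that the data cannot answer.** The stated objectives concern 6–36 months, and the design can address them. Length at entry also reflects growth up to that age.
- **No visit window.** An article may leave this to the full protocol, so its absence is no finding. A tolerance would also have to be large: at least 1 month for the first child and 3–4 months for the last under the assumption above.

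**Conclusion.** The contradiction stands. The stated months allow at most 17.0 months for all main-study data collection against an 18-month interval, so the end-line visit as described is unreachable for every child. This part needs no assumption.

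The larger figures rest on an assumed baseline round of 2–3 months from 1 April 2024. The last children would then have at most about 14–15 months by the closing date; with 18 months kept, the last visits would fall at about the end of November to the end of December 2025. A reader might infer that this overshoots the dissemination date. The document gives only the month of December 2025, so the supported statement is that little or no time is left for analysis.

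The abstract's age window is wrong for this design. It is most plausibly a slip for 18 months of follow-up, which is how the objectives word the goal.

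**What to change.** Reconcile Objectives, Study design and data collection, and Study timeline in one of two ways:

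1. Keep 18 months, and restate the close of data collection as at least 18 months after the last baseline visit, with dissemination moved to match. With a 2–3 month baseline, keeping the present gap of 3–4 months would put dissemination at about the end of February (end of November + 3 months) to the end of April 2026 (end of December + 4 months).
2. Keep the dates, and restate the follow-up length and the end-line age range that the calendar allows.

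If the intervals then differ between children, include each child's actual follow-up time in the change-in-HAZ model. Both visit dates will be on record, so this needs no new data.

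In the abstract, replace the age window in both places with the range actually observed: 6–36 months, or the revised range under the second option.

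The cost is a change of wording, plus either later reporting or a slightly shorter stated follow-up.
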